### 3 STUDY DESIGN

This will be a randomised, controlled, double blind trial with three arms including: 10 children to receive 30µg GMZ2, 10 children to receive 100µg GMZ2 and 10 children to receive rabies vaccine.

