## **3.5 Treatment Assignment Procedures**

### **3.5.1 Randomization Procedures**

Individual participants will be randomized to receive either 30µg or 100µg of GMZ2 or rabies vaccine. Randomization to any of the three groups will be done based on a list of eligible participants identified after screening is completed. The randomization list generated by the statistician will ensure that the random allocation has a fairly even distribution of sex and age in the groups. The randomization list will contain sequential codes linking a study number to a vaccine assignment. Study numbers will be assigned to participants of each cohort in the order in which they are enrolled in the trial. Access to the randomization list will be exclusively limited to the vaccine administrator/pharmacist(s) and the study statistician. These individuals will be unblinded and will not be involved in any of the study participants' evaluation. The independent Local Safety Monitor will also keep one set of the randomization code in a sealed envelope, for the event when emergency unblinding may be required.

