## 5 PARTICIPANT PROCEDURES

### 5.1 Screening Day –14 to –1

The accepted process of reaching the community that has been established over the years between MRU and Lambaréné community will be followed. This requires that after the protocol is approved by the authorities, special information dissemination meetings are held starting with the key civic and traditional leaders. Awareness campaigns are then undertaken including peer communication groups before the reaching the stage of small groups of potential participants, and finally individuals.

After community information is disseminated as described, all interested guardians of potential participants will be invited to visit the study clinic on a specific date. They will receive oral and written explanation of the study, after which the screening consent will be obtained from those willing to participate. After the study has been explained to the parents/guardians of potential participants, they will be free to leave and return later with their decision; this will allow time for them to discuss the study with their family and carefully consider their involvement in the study.

All screening tests, medical history and examinations will be performed only after screening consent is obtained. Clinical Investigators will generally handle acute, simple conditions such as malaria or other acute infections. More complicated or chronic conditions, such as chronic renal or heart disease, will be referred to appropriate sources of medical care.

It is estimated that 50-60 children will be screened in order to obtain a list of at least 40 eligible participants. Participants will be recruited among children residing in Lambaréné.

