## 5.2 Enrolment/Baseline

When a total of 40 eligible participants are screened, a list with their screening numbers, dates of birth and sex will immediately be generated and transmitted to the study statistician based at the London School of Hygiene and Tropical Medicine. The statistician will then generate a randomisation code list that allocates study ID numbers linked to vaccine allocation. This list will be generated to ensure that an even distribution of age and sex is achieved in each of the three study groups. The statistician will then send the randomisation code list directly to the study pharmacist and local safety monitor via email with a secure password to access the list.

At the site study numbers will be assigned to participants of each cohort in the order in which they come to MRU on the day of the first vaccination. Immediately after the first vaccination, each study participant will receive a photo ID card and a copy of the photo ID will be attached to the CRF folder for each participant. The vaccine and dose that are assigned during the first vaccination will be maintained for second and third vaccinations.

Access to the randomization list will be exclusively limited to the study drug manager(s)/pharmacist(s) and study statistician. These individuals are unblinded and will not be involved in study participants' further evaluation. The Local Safety Monitor will also keep one set of the randomization code in a sealed envelope, in the event that emergency unblinding is required. The reason for any unblinding will be documented as well as the steps to be taken.

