### 8.2 Determination of the Sample Size

The total number of participants will be 30 divided into three groups of 10 each; one receiving 30 µg of GMZ 2, another 100 µg of GMZ2 and the other receiving rabies vaccine (control vaccine). The sample size chosen for this study are in line with similar safety and immunogenicity studies of similar candidate malaria vaccines published in the literature. As a phase I protocol, this study of 30 volunteers is not designed to detect adverse reactions that occur infrequently. Sample size was determined by the requirement to make a preliminary evaluation of inter-group and inter-individual variability, to avoid excessive risk and to allow realistic workload. Statistical significance may not be reached in such a study with low power; however, a non-significant finding would provide justification of the need for a study with greater power.

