### 8.3 Data Set to be analysed

#### 8.3.1 Definition of Population

Given the above mentioned considerations it is planned to enrol 30 participants in the trial, to be randomised into the three treatment arms.

The statistical analysis shall be performed on two types of population depending on the participant's compliance to the protocol:

**i). Per Protocol:** the vaccination, blood sampling and visits number as well as the time-interval between vaccination and follow-up visits are respected, as they are defined in the protocol and in the flow chart. All participants who have not been compliant with the protocol will be excluded from this analysis but will be described in the final report. The protocol compliance criteria are the following:

- Participants fulfilling the inclusion and exclusion criteria
- Participants who have respected the number of vaccination and the time-intervals between the vaccination:
  - V2: 1st vaccination: D0, interval V1+2 weeks (± 3days)
  - V7: 2nd vaccination D28 , interval V2+4 weeks (± 3 days)
  - V12: 3rd vaccination D56 , interval V5+4 weeks (± 3days)
  - V17: Post vaccination D84 , interval V12+4 weeks (± 7days)
  - V18: Last study visit D365 , interval V17+ 9months (± 14days)
  - Subjects having respected the number of blood samples for biological safety evaluation, as well as the intervals between blood samples on Days -14, 28, 56, 84 and 365 within their applicable intervals

[figure not shown]

**ii). Intention to treat:** All participants who have received at least one vaccine dose will be included in the analysis. However, if a participant is not vaccinated for reasons unrelated to the primary outcome measure and the participants' code was broken during the period of the study that participant will be excluded from further analyses. In the event a participant withdraws from the study due to side effects, the last observation will be carried forward in all subsequent analyses (Last Observation Carried Forward LOCF) of the primary outcome measure.

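### The age- and sex-balanced randomisation list is filled by order of arrival, so the stated procedure leaves the promised balance to chance; how 30 children are taken from 40 is also unstated

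*Protocol*

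**What the plan says.** Section 5.1 expects that "50-60 children will be screened in order to obtain a list of at least 40 eligible participants". Section 5.2 continues: "When a total of 40 eligible participants are screened, a list with their screening numbers, dates of birth and sex will immediately be generated" and sent to the statistician, who returns a code list linking study ID numbers to vaccines. Of that list it says: "This list will be generated to ensure that an even distribution of age and sex is achieved in each of the three study groups". Section 3.5.1 makes the same promise more softly (fairly even) and describes the list as sequential codes that connect a study number to a vaccine.

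On how a child obtains a study number, section 5.2 says "At the site study numbers will be assigned to participants of each cohort in the order in which they come to MRU" on the first vaccination day. Section 3.5.1 says "Study numbers will be assigned to participants of each cohort in the order in which they are enrolled in the trial". Neither section defines *cohort*. The synopsis row on allocation concealment gives a third description: sealed envelopes prepared by the statistician from the screened list of eligible children. Section 4.1.4 confirms that the content of the syringe follows the study ID number.

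On numbers, section 8.2 says "The total number of participants will be 30 divided into three groups of 10 each", section 3 has "10 children to receive 30µg GMZ2, 10 children to receive 100µg GMZ2 and 10 children to receive rabies vaccine", and section 8.3.1 says "it is planned to enrol 30 participants in the trial, to be randomised into the three treatment arms".

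**The concern.** Dates of birth and sex can balance the arms only if each code is reserved for a particular child, or for children of a particular age and sex. The protocol collects these data, uses them to build the list, and then issues the codes by a rule that ignores them. The list may be perfectly balanced on paper for 40 known children, but once codes are taken in queue order that balance no longer applies to the children who receive them.

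This matters because section 1.8.3 wants to detect dose-dependent toxicity with 10 children per arm, and section 8.6 presents results by group. The solicited systemic reactions in section 6.3.2 are partly graded on crying, drowsiness and appetite in children aged 1 to 5. It is plausible that these vary with age, though the protocol gives no figures. A chance difference in age or sex between arms could then be read as a dose effect. An analysis plan cannot restore balance after the first vaccination.

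**Working it through.** **1. The plan's own figure.** 3 × 10 = 30, which agrees with sections 3, 8.2 and 8.3.1. The list sent to the statistician has 40 children, and 40/3 = 13.33, so those 40 cannot be split equally into three arms.

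**2. Does the procedure use age and sex?**

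| Step | Source | Uses the child's age or sex? |
|---|---|---|
| Dates of birth and sex sent to the statistician | 5.2 | Yes |
| List made even for age and sex | 3.5.1, 5.2 | Yes, as intended |
| List links study number to vaccine | 3.5.1, 5.2 | No link to a screening number is stated |
| Child receives a study number | 5.2 (arrival), 3.5.1 (enrolment) | No |
| Syringe content follows study number | 4.1.4 | No |

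The chain from a child's age and sex to the arm breaks at the third and fourth steps.

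**3. Sex balance left to chance.** Assumptions, not in the protocol: 15 boys among the 30 vaccinated, and arms of exactly 10. With a, b and c boys in the three arms and a + b + c = 15,

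P(a, b, c) = C(10,a)·C(10,b)·C(10,c) / C(30,15).

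- Exactly 5/5/5: 252³ / 155,117,520 = 16,003,008 / 155,117,520 = 10.3%.
- Some arm with 3 or fewer, or 7 or more, boys (7:3 or worse): summing the formula over those outcomes gives 46.7%.
- Arms differing by 4 or more boys: 26%.

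If the 30 are instead a random draw from 40 children of whom 20 are boys, arms differ by 3 or more boys in 51% of draws and by 4 or more in 26% (simulation).

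**4. Age balance left to chance.** The age distribution is also an assumption. The probability that the largest and smallest arm mean ages differ by at least 1 year, by simulation with arms of 10, is:

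| Assumed ages | P(gap ≥ 1 year) |
|---|---|
| Continuous, even over 1 to 5 years | 13–16% |
| Continuous, even over 1 to under 6 years | 27–32% |
| Whole years, six children at each of 1 to 5 | 31% (24% if gaps of exactly 1 year are excluded) |

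The ranges in the first two rows reflect whether ages are drawn at random or spaced evenly. The inclusion criterion, 1 to 5 years inclusive, can be read either way. For random draws over 1 to under 6 years the median gap is 0.73 years.

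**5. Arm sizes.** These depend on the list, not on arrival order.

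- 30 codes, 10 per arm: 10/10/10 in any order of arrival.
- 40 codes in permuted blocks of 3 or 6, first 30 used: 30/3 = 10 and 30/6 = 5 complete blocks, so 10/10/10.
- Unblocked codes, or blocks that do not end at 30: 10/10/10 is not assured.

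The protocol does not say which applies.

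**The case against.** The best defence lies in the word *cohort*. If it means an age-sex group with its own run of study numbers, assigning by arrival within each cohort keeps the balance. The synopsis wording (envelopes based on the screened list) and the reference in 3.5.1 to a list of eligible participants also hint at allocation by child. The reading is possible, but the protocol defines no cohort, stratum or age band, and no section connects a code to a screening number. What survives is that the intended procedure may be sound; the written one is not.

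A second defence is that assignment by arrival from a concealed list is valid randomisation and that section 8.6 is descriptive. Both points stand. A reader might infer that the trial is biased or its randomisation broken; the documents do not support that. Baseline antibody and laboratory values are measured too, and section 3.5.1 promises only a fairly even distribution. These points lower the weight of the problem. But section 8.6.2 still intends the groups' immunogenicity to be compared, so balance is not irrelevant.

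A third is that list length and block size are commonly settled outside the protocol. That is fair for block size. It does not cover the step from 40 listed to 30 enrolled, because the protocol describes that step and gives no rule for it.

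**Conclusion.** The point stands as a mismatch between a stated property and the stated procedure. As written, age and sex do not influence allocation, and sections 3.5.1 and 5.2 and the synopsis describe the mechanism in three ways. The loss is the promised balance, not validity. Its size under the stated assumptions is a 7:3 or worse sex split in some arm in about 47% of draws, exact 5/5/5 in about 10%, and a mean-age gap of a year or more in about 13% to 32%. None of these inputs comes from the protocol, so the figures show scale and are not forecasts.

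A reader might go further and infer that 10/10/10 will not be achieved. If 40 unblocked codes split 14/13/13 were cut at 30, the chance of 10/10/10 would be C(14,10)·C(13,10)²/C(40,30) = 1001 × 286² / 847,660,528 = 9.7%, with arms differing by 3 or more in 49%. The documents do not support that inference: no section describes such a list, section 5.2 lists 40 children and not 40 codes, and the simple designs above give 10/10/10 exactly. The accurate statement is that the text does not guarantee it.

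For a small, descriptive phase I trial this should be corrected before the first vaccination, but it would not invalidate the trial.

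**What to change.** Choose one mechanism and describe it identically in the synopsis, 3.5.1 and 5.2.

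- **Option A.** The statistician ties each study number and vaccine in advance to one screening number for 30 selected children, stratified by sex and age band, with 10 per arm in total. The other 10 are reserves in a fixed order; a reserve replaces a no-show only within the same stratum and takes over that allocation. Arrival order then plays no part and its wording is removed.
- **Option B.** Issue a separate blocked code sequence for each age-sex stratum and assign by arrival within stratum. The arrival wording stays, with *cohort* replaced by the defined stratum. For exactly 10/10/10 with blocks of three, the number enrolled in each stratum should be a multiple of three (for example 9 + 6 + 9 + 6 = 30).

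Under either option, define the age bands, state how 30 are taken from the 40 listed, and state how many codes are issued. The codes should remain with the unblinded pharmacist, the statistician and the sealed copy of the Local Safety Monitor, as now planned.

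The cost is reworded text and a different list format before Day 0, with no added children, visits or staff. The change cannot be made once vaccination has started.

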## 5.3 Vaccination process

Before each vaccination, exclusion criteria will be reviewed and verified. A history-directed physical examination will be done and temperature and baseline general symptoms/signs will be recorded.

After the participant's identity is checked by comparing his name with the list of eligible volunteers, vaccination will be administered by intramuscular injection into the left deltoid muscle. If any local impairment prevents administration of the vaccine into the preferred deltoid for that particular vaccination, the vaccine may be administered into the opposite deltoid, and accordingly documented. Vaccination will be done on study days 0, 28 +/- 3 and 56 +/- 3.

### Day 0: Vaccination 1 - Visit 2

**Before vaccination** the following steps will be taken:

- Countercheck to confirm the identity of the participant
- Review screening laboratory test results
- Review inclusion/exclusion criteria and check of contraindications/precautions
- Record any complaints, symptom-directed physical examination, and examination of the injection site(s) for any abnormalities
- Record vital signs: tympanic temperature

[figure not shown]

- Collect 7.5 ml venous blood sample to measure:
  - FBC (EDTA) 2.5 ml.
  - Biochemistry, WB, ELISA, and GIM (Serum) 2.5 ml.
  - Peripheral blood mononuclear cells (PBMC) for memory B-cell ELISPOT 2.5 ml
- Give time to calm the child after the blood draw
- Administer the vaccination dose 1 according to SOP
- Assignment of unique study number

**After vaccination** the following steps must be taken:

- Observe for a minimum of 30 minutes
- Record tympanic temperature
- Assessment of the immediate local and systemic solicited events
- Prepare an ID card containing participant's unique study number and photo
- Ensure that the copy of the ID photo is attached to the participant's CRF
- Provide further information on when the next visit should be
- Instruct the guardian to return to the MRU centre immediately should the participant manifest any signs or symptoms they perceive as important.

#### **Days 1: Post-vaccination 1 surveillance clinic visit**

##### **Visit 3**

- Verify and confirm ID of the participant
- Review history for any adverse events
- Targeted physical examination for solicited local and systemic symptoms
- Record tympanic temperature
- Record other signs/symptoms
- Give details of next visit and remind guardian on what to do if case of any problem

#### **Day 3: Post-vaccination 1 surveillance clinic visit**

##### **Visit 4**

- Verify and confirm ID of the participant
- Review history for any adverse events
- Targeted physical examination for solicited local and systemic symptoms
- Record tympanic temperature
- Record other signs/symptoms
- Give details of next visit and remind guardian on what to do if case of any problem

#### **Days 2- 6: Post-vaccination 1 surveillance home visits on days 2, 4, 5 and 6**

##### **Field worker home visits**

- Complete the field worker home visit card information
- Solicited symptoms
- Record tympanic temperature
- Record any adverse events occurring after the previous study vaccination
- Provide details on next visit and what to do in case of any problem

[figure not shown]

**Day 7± 1 day: Post-vaccination 1 surveillance visit**  
**Visit 5**

- Verify and confirm ID of the participant
- Review history for any adverse events
- Targeted physical examination for solicited local and systemic symptoms
- Record tympanic temperature
- Record other signs/symptoms
- Give details of next visit and remind guardian on what to do if case of any problem

**Day 14± 2 days: Post-vaccination 1 surveillance visit**  
**Visit 6**

- Verify and confirm ID of the participant
- Review history for any adverse events
- Targeted physical examination for solicited local and systemic symptoms
- Record tympanic temperature
- Record other signs/symptoms
- Give details of next visit and remind guardian on what to do if case of any problem

**Day 28± 3 days: 4 weeks post-vaccination 1 surveillance visit and vaccination 2**  
**Visit 7**

**Before vaccination** the following steps will be taken:

- Countercheck to confirm the identity of the participant
- Review inclusion/exclusion criteria and check of contraindications/precautions
- Record any complaints, symptom-directed physical examination, and examination of the injection site(s) for any abnormalities
- Record vital signs: tympanic temperature
- Collect 5 ml venous blood sample to measure:
  - FBC (EDTA) 2.5 ml.
  - Biochemistry, WB, ELISA, and GIM (Serum) 2.5 ml.
- Give time to calm the child after the blood draw
- Administer the vaccination dose 2 according to SOP

**After vaccination** the following steps must be taken:

- Observe for a minimum of 30 minutes
- Record tympanic temperature
- Assessment of the immediate local and systemic solicited events
- Provide further information on when the next visit should be
- Instruct the guardian to return to the MRU centre immediately should the participant manifest any signs or symptoms they perceive as important.

**Days 29: 1 day, post-vaccination 2 surveillance clinic visit**  
**Visits 8**

- Verify and confirm ID of the participant

[figure not shown]

- Review history for any adverse events
- Targeted physical examination solicited local and systemic symptoms
- Record tympanic temperature
- Record other signs/symptoms
- Give details of next visit and remind guardian on what to do if case of any problem

**Days 31: 3 days post-vaccination 2 surveillance clinic visit**

**Visit 9**

- Verify and confirm ID of the participant
- Review history for any adverse events
- Targeted physical examination for solicited local and systemic symptoms
- Record tympanic temperature
- Record other signs/symptoms
- Give details of next visit and remind guardian on what to do if case of any problem

**Days 30-34 Post-vaccination surveillance home visits on days 30, 32, 33, and 34**

*Field worker home visits*

- Complete the field worker home visit card information
- Solicited symptoms
- Record tympanic temperature
- Record any adverse events occurring after the previous study vaccination
- Provide details on next visit and what to do in case of any problem

**Day 35± 1 day: 7 days post-vaccination 2 surveillance visit**

**Visit 10**

- Verify and confirm ID of the participant
- Review history for any adverse events
- Targeted physical examination for solicited local and systemic symptoms
- Record tympanic temperature
- Record other signs/symptoms
- Give details of next visit and remind guardian on what to do if case of any problem

**Day 42± 2 days: 14 days post-vaccination 2 surveillance visit**

**Visit 11**

- Verify and confirm ID of the participant
- Review history for any adverse events
- Targeted physical examination for solicited local and systemic symptoms
- Record tympanic temperature
- Record other signs/symptoms
- Give details of next visit and remind guardian on what to do if case of any problem

[figure not shown]

